### Objectives {7}

Our primary objective is to test whether psilocybin (prior to adjunctive psychotherapy) leads to significant acute and subacute changes in functional brain activity in networks associated with mood regulation and depression compared to placebo and supportive therapy. We hypothesize that regional CBF will be modulated during the acute phase of treatment relative to placebo, particularly in brain networks associated with mood regulation and depression. Specifically, there will be an acute increase in dorsolateral prefrontal cortex blood flow and a reduction in the subgenual anterior cingulate cortex blood flow between baseline and the first active treatment (Treatment Visit 1). The CBF findings will be contrasted against resting-state fMRI data. Our secondary objective is to examine whether participants treated with psilocybin-assisted psychotherapy will have a greater reduction in depression scores over time signified by the MADRS relative to those who receive placebo. Our secondary hypothesis is that a reduction in MADRS score will be related to an increase in dorsolateral prefrontal cortex blood flow and a decrease in subgenual anterior cingulate cortex blood flow between baseline and the first treatment visit among participants treated with psilocybin compared to placebo. Additionally, our exploratory objective will examine blood biomarkers that are mechanistically related to psilocybin and/or MDD including those involved with increased neurogenesis and neuroplasticity (BDNF), glial pathology (S100B), and systemic inflammation (CRP). It is predicted that these biomarkers will be associated with MADRS scores at baseline. Our exploratory hypothesis is that our baseline blood-based biomarkers of interest will predict treatment response (i.e., changes in depression scores) measured over time by the MADRS. It is expected that there will be a post-treatment increase in BDNF and a reduction in CRP and S100B plasma levels.

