### Outcomes {12}

Exploratory imaging analysis will consist of voxel-wise analyses to fully characterize regional group and session effects. These analyses will probe circuit-based perspectives by considering the following four relevant resting-state networks: (1) salience, (2) left frontoparietal, (3) right frontoparietal, (4) default mode brain regions. Furthermore, we will conduct brain and behavioural responses, namely regional CBF changes in relation to the MADRS scores. Well-validated markers of brain neuroplasticity (BDNF), systemic inflammation (CRP), and glial pathology (S100B) will be measured in blood at baseline and subsequently evaluated as predictors of treatment response.

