## Data collection and management

### Plans for assessment and collection of outcomes {18a}

The assessments to be collected for both primary and secondary outcomes can be found in Table 2. For each participant, much of the data will be securely stored in the form of an electronic case report form (eCRF) which will include participant demographics, clinical scales and assessments, medical information including any pre-existing conditions and history, concomitant medications and therapies, vital signs (i.e., ECG, blood pressure), baseline blood tests, follow-up visits, any AEs or SAEs (if applicable), documentation of a participant’s informed consent, study visit dates, participant identification numbers, and any documentation pertaining to the appropriate data entry, management, validation, and archival. Paper-based copies of study questionnaires will be kept in the physical CRF with the unique, anonymized identification number assigned to a given participant and securely stored on-site in an area with restricted access at the hospital. Participant data captured during the trial will only be identified by a participant ID and managed in the electronic CRF (eCRF) that will be securely stored in online Research Electronic Data Capture (REDCap) software. REDCap is a secure, web-based software that is designed to support data capture for clinical trials and research studies. MRI data will be stored on a secure research server at Sunnybrook Health Sciences Centre. All questionnaires used in the study have been previously published and validated for research and/or clinical use. The ASL and MRI techniques have been previously published and validated.

**Table 2 Tab2:** Primary and secondary outcomes

**Primary outcomes**	• Significant alterations in regional CBF across three a priori brain regions from baseline to treatment visit 1
	• Improvement in depressive symptoms using the Montgomery-Asberg Depression Rating Scale (MADRS) from baseline to week 3 and week 6 following initial psilocybin/placebo administration. Higher scores with respect to the MADRS minimum (0) and maximum (60) values represent a worse treatment outcome [89]

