## Statistical methods

### Statistical methods for primary and secondary outcomes {20a}

The primary and secondary analyses will be conducted at Sunnybrook Health Sciences Centre, using open-source software tools, to the extent it is possible. Image processing will be conducted by a trained individual who will remain blind to the treatment allocation throughout the data analysis period. We propose to analyze our primary outcome using mixed-effects linear regression to measure CBF changes across our regions of interest from Baseline to Treatment Visit 1, as well as MADRS changes from Baseline, Week 3, and Week 6 following administration. A priori CBF regions consist of emotion regulation regions that are disrupted in MDD [109, 110], comprising the dorsolateral prefrontal cortex, salience network regions comprising the insula cortex, and default mode network comprising the parietal precuneus.

We will determine an optimal model for data analysis by fitting the model described in Eq. 1 to data using the *lme4* package in R, as well as additional models adding interaction effects of age, sex, and number of prior failed antidepressant treatments with drug to assess whether demographics or treatment-resistance modify the effect of psilocybin. An optimal model will be selected by comparing models fit by maximum likelihood estimation using a chi-squared test of model deviance. This will provide the added benefit of further robustness against the possibility of model non-convergence. As described in the sample size calculation, marginal means of a Visit x Drug interaction will be estimated using the *emmeans* package in R, and two within-subject contrasts of baseline to treatment visit 1 change in CBF will be calculated as well as a between-subject difference in these contrasts. Sidak’s correction for multiple comparisons will be applied to adjust *p*-values, with the primary outcome measure being the between-subject difference in the change in CBF attributable to psilocybin vs placebo at treatment visit 1.

For our exploratory analysis, peripheral levels of S100B, BDNF, and CRP will be measured using standard enzyme-linked immunosorbent assays or similar multiplexed immunoassay. All data analyses will be performed using SPSS 22.0. Multivariate linear regression analysis will be used to assess the relationship between baseline and change in peripheral biomarker measures and post-treatment change in MADRS scores.

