### Methods for additional analyses (e.g., subgroup analyses) {20b}

We will perform sensitivity analyses to evaluate the relationship between sex and the primary outcome measures. No additional analyses are planned.

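### The Objectives predict a change in subgenual anterior cingulate blood flow, but the three primary CBF regions leave that region out, so the prediction has no named primary or secondary analysis

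*Protocol article*

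**What the plan says.** **Objectives {7}.** After a general hypothesis that regional CBF will change relative to placebo, particularly in mood-related networks, the text becomes specific: "there will be an acute increase in dorsolateral prefrontal cortex blood flow and a reduction in the subgenual anterior cingulate cortex blood flow", from baseline to Treatment Visit 1. The secondary hypothesis relates MADRS reduction to a DLPFC increase and to "a decrease in subgenual anterior cingulate cortex blood flow between baseline and the first treatment visit among participants treated with psilocybin compared to placebo".

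**Table 2 (section {18a}).** The first primary outcome is "Significant alterations in regional CBF across three a priori brain regions from baseline to treatment visit 1". The table does not name the regions.

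**Statistical methods {20a}.** The a priori regions are named here: "comprising the dorsolateral prefrontal cortex, salience network regions comprising the insula cortex, and default mode network comprising the parietal precuneus".

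**Outcomes {12}.** "Exploratory imaging analysis will consist of voxel-wise analyses to fully characterize regional group and session effects", organised around four networks: "1) salience, (2) left frontoparietal, (3) right frontoparietal, (4) default mode brain regions". The same section plans to relate regional CBF changes to MADRS without saying which regions.

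**Additional analyses {20b}.** Sensitivity analyses for sex, then "No additional analyses are planned".

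**Sample size {14}.** The simulation uses one generic CBF value that rises by 23% (SD 23%) under psilocybin.

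**The concern.** The subgenual ACC is named only in the Objectives. It appears in no outcome, region list or analysis section. An analyst who follows {20a} and Table 2 will estimate the treatment contrast in DLPFC, insula and precuneus and will produce no named result for one of the two regions that the trial specifically predicts. The secondary hypothesis has the same gap, because it needs a subgenual ACC measure and no analysis section supplies one.

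The mismatch also weakens interpretation. Suppose DLPFC is null and insula is positive: the primary outcome as listed shows an alteration, although no direction was predicted there. Suppose instead that subgenual ACC turns up in the voxel-wise maps: a report could present this as the stated hypothesis confirmed. The Limitations section relies on a priori regions to strengthen the primary imaging analysis, and that works only if the hypotheses and the region list agree.

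**Working it through.** **1. The two lists side by side**

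| Region | Specific prediction in {7} | Primary region in {20a} |
|---|---|---|
| DLPFC | increase | yes |
| Subgenual ACC | decrease | no |
| Insula | no direction stated | yes |
| Precuneus | no direction stated | yes |

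One of two directional predictions (1/2) has no matching primary test. Two of three primary regions (2/3) have no direction.

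**2. Can the lists be read as one?** Section {20a} describes its salience component by the insula and its default mode component by the precuneus. With DLPFC these make exactly the three regions that Table 2 counts, so there is no room for a fourth. The voxel-wise work in {12} is labelled exploratory and does not name the subgenual ACC. Section {20b} adds only sex.

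**3. The protocol's power figure.** Section {14} states more than 80% power with 20 per group. Inputs from {14}: baseline 55 (SD 13), test-retest variability 3%, effect 23% (SD 23%) of baseline. For each of 4,000 simulated trials:

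- d = (mean change on psilocybin) − (mean change on placebo), Treatment Visit 1 minus baseline
- t = d / √(4s²/n), with s² the within-subject residual variance on 2(n − 1)(T − 1) degrees of freedom, n per group and T visits; two-sided

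Power at n = 20:
- three visits, unadjusted: 92%
- two visits, Sidak over three tests: 96%
- closed form, Sidak over three tests: 97%
- three visits, Sidak over three tests: 77.5%

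The last is the only one below 80%. With the protocol's 500 simulated datasets the Monte Carlo standard error is √(0.775 × 0.225 / 500) = 1.9 points, so it lies about 1.35 standard errors below 80%. The stated figure is reproduced for one generic region.

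**4. Cost of a fourth region.** The protocol does not state the Sidak family; it mentions the correction next to the contrasts. Two assumptions, with per-test alpha = 1 − 0.95^(1/k) and power for three visits at 25 per arm:

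| Assumed family | k with 3 regions: alpha, power | k with 4 regions: alpha, power |
|---|---|---|
| Regions only | 3: 0.0170, about 89% | 4: 0.0127, about 86% |
| Regions × 3 contrasts | 9: 0.0057, about 78% | 12: 0.0043, about 72% |

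These powers assume a 23% effect (SD 23%) in each region.

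**5. Power for a subgenual ACC decrease.** The documents give no effect size for it, so a range is needed. At 25 per arm and alpha 0.0170:
- decrease of 23% (SD 23%): 90%
- decrease of 15% (SD 15%): 88%
- 15% with the SD kept at 23%: 38% (run as an increase; the test is two-sided, and the 23% and 15% runs with equal SD gave nearly the same power in either direction)

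All of these figures illustrate cost. The mismatch itself does not depend on them.

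**The case against.** The strongest reply is that the governing hypothesis is general. It predicts modulation in mood-related networks, and all three regions in {20a} test it. Section {20a} describes them as emotion regulation regions disrupted in depression, and the Background argues separately for studying default mode regions. Table 2 asks only for alterations, so a primary region needs no direction. For the listed primary outcome, Table 2 and {20a} agree. The protocol is a journal article, and a fuller analysis plan may exist.

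Much of this stands, and it rules out some stronger readings. A reader might infer that half of the primary hypothesis is never tested. The documents do not support that: the general statement is tested through the three regions, and the voxel-wise maps may reach the subgenual ACC. A reader might infer that insula and precuneus are tested without any hypothesis. They lack a direction, not a rationale. A reader might infer that two competing primary region lists allow a free choice after the data are seen. No outcome or analysis section offers a second list; the risk is the narrower one that a report leans on whichever statement suits the result.

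The reply does not remove the mismatch. Condensing a protocol can explain a missing detail but not two statements that disagree, and an unseen analysis plan could match only one of them.

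**Conclusion.** The point holds as a contradiction within the article. The Objectives name DLPFC and subgenual ACC; the primary analysis names DLPFC, insula and precuneus. The subgenual ACC prediction, in both the primary and the secondary hypothesis, has no named analysis and at most exploratory coverage. Insula and precuneus are primary regions without a stated direction. This rests on the text alone.

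The drop in per-test alpha from 0.0170 to 0.0127 should not be read as a property of the current plan. It assumes a Sidak correction across regions, which the protocol does not state. The accompanying power figures also assume a subgenual ACC effect as large as the generic 23%, which the documents do not support with any figure.

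**What to change.** Before unblinding, make Objectives {7}, Table 2 and section {20a} name the same regions.

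- **Preferred:** add subgenual ACC as a fourth a priori region in {20a} and Table 2, with the predicted decrease. Name DLPFC and subgenual ACC as the regions for the CBF-MADRS analysis. State a direction for insula and precuneus, or state that they are tested without one. State the family over which Sidak is applied (regions, contrasts or both).
- **Alternative:** revise the hypotheses in {7}, including the MADRS hypothesis, to match the three listed regions, and label subgenual ACC as exploratory.

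The preferred change costs one more region taken from ASL maps that the protocol already plans to acquire, some wording, and the small loss of power shown above if the correction runs across regions. It also leaves a gap to acknowledge: the simulation in {14} models a generic increase and gives no power basis for a subgenual ACC decrease, so an assumed effect and SD for that region should be stated. The alternative costs only wording but gives up a confirmatory answer on the subgenual ACC.

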
### Sample size {14}

As this study will employ a longitudinal design with multiple visits where CBF measurements in individual subjects may reasonably be expected to be highly dependent across visits, we will model use linear mixed-effects models of CBF at all visits to account for effects of psilocybin and MCC placebo independently of baseline CBF. Specifically, we will use the following model (in *lme4* syntax):1$$CBF\sim Age+Sex+Drug+Drug\;x\;Visit+(\mathit1\;\vert\;ID)$$

To assess the difference in CBF associated with psilocybin relative to placebo, marginal means of a Visit x Drug interaction will be calculated using the *emmeans* package in R, and contrasts between baseline and treatment visit 1 CBF under psilocybin and placebo conditions will be calculated separately, and an additional contrast composed of the difference of these two contrasts will be calculated. Sidak’s correction for multiple comparisons will be used to adjust *p* values. The primary endpoint will be the contrast estimating the between-group difference in within-subject differences in psilocybin- and placebo-induced CBF changes at treatment visit 1 vs baseline (i.e. [V1 psilocybin − V0] − [V1 placebo − V0]).

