As a power analysis, we simulate 500 datasets each for groups of size *N* = 5 − 50, in increments of 5. For each simulated subject, baseline CBF is sampled from a normal distribution 55 ± 13 mL/100/g min. At each subsequent visit, a ± 3% test-retest variability is added to the baseline CBF. At psilocybin visits, relative to subject-specific baseline CBF, a proportional 23% ± 23% increase in CBF is added. MCC placebo has no direct psychotropic effects. For each of these 500 datasets, a model (Eq. 1) is fit to the data, and the contrasts described above are calculated. Sufficient power is achieved when evaluation of the between-group contrast of interest for a given group size produce corrected *p*-values below *α* = 0.05 at a frequency equal to or greater than a pre-specified power of 80%. This power analysis suggests two groups of *N* = 20 are sufficient to reject the null hypothesis in > 80% of cases. Sensitivity analyses additionally suggest that sufficient power can be achieved with *N* = 25 in each group if test-retest variability is as high as 7.5%, or if psilocybin effect size and variance is scaled from 23% to as low as 15% [see Additional file 3]. As these simulated datasets are likely somewhat idealized relative to real-world data, we will use a total of *N* = 50 subjects with 25 allocated to each arm.

These anticipated CBF group session differences are consistent with a recently conducted acute neuroimaging clinical trial in bipolar depression [82]. Although we do not conduct a power analysis for H_A,2_, we provide context from the literature in support of the MADRS outcome measure. Example studies incorporating the MADRS outcome measure are provided [see Additional file 4], showing trial design, sample sizes, intervention details, and the reported changes in MADRS score [83–87].

Thus, our MADRS assessments for *N* = 50 is consistent with previous depression trials and support our second hypothesis (H_A.2_).

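### If Drug is the randomised arm, the planned covariate-by-Drug terms cancel from the baseline-to-visit-1 change and barely test effect modification; the protocol does not define the coding of Drug

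*Protocol article*

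**What the plan says.** Eq. 1 of the protocol article (Sample size {14}) is CBF ~ Age + Sex + Drug + Drug × Visit + (1 | ID). From its Visit × Drug marginal means, "contrasts between baseline and treatment visit 1 CBF under psilocybin and placebo conditions will be calculated separately", and a further contrast takes their difference. The same section fixes the target: "The primary endpoint will be the contrast estimating the between-group difference in within-subject differences in psilocybin- and placebo-induced CBF changes", at treatment visit 1 against baseline, that is [V1 psilocybin − V0] − [V1 placebo − V0].

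Statistical methods {20a} starts from Eq. 1 and brings in "additional models adding interaction effects of age, sex, and number of prior failed antidepressant treatments with drug". The stated purpose is "to assess whether demographics or treatment-resistance modify the effect of psilocybin". The choice among models is then made as follows: "An optimal model will be selected by comparing models fit by maximum likelihood estimation using a chi-squared test of model deviance".

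No term crossing a covariate with both Drug and Visit is described. Methods for additional analyses {20b} offers a sensitivity analysis on sex, without giving its form, and rules out anything further. Age and number of failed treatments therefore have no other route. Neither section states whether Drug means the randomised arm or the treatment received at a visit.

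**The concern.** The quantity of interest is a change within participants compared between arms. In Eq. 1 that comparison lives in Drug × Visit, so a covariate modifies it only through a covariate × Drug × Visit term. The terms described are one order short. If Drug is the arm, they let the covariate slope of the CBF level differ between arms, by the same amount before and after dosing, and the fitted drug effect is forced to be identical at every age, in both sexes and for any number of failed treatments.

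Two errors could follow. A real modifier would usually be missed and reported as absent. A chance difference between arms in the covariate slope of CBF, which can already be present before dosing, could be reported as modification of the psilocybin effect.

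**Working it through.** **Inputs from Sample size {14}.** "baseline CBF is sampled from a normal distribution 55 ± 13 mL/100/g min"; 3% test-retest variability; psilocybin effect 23% ± 23% of the participant's own baseline; α = 0.05 after Sidak correction; 25 per arm. Assumptions not in the documents: Sidak is applied over three contrasts, tests are two-sided, and one SD of age shifts the psilocybin response by m = 10, 15 or 20 percentage points.

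**The plan's own figure.** Refitting Eq. 1 with Drug as arm, three visits, 500 datasets per size and each participant's drug effect shared across visits gives power of 51%, 77%, 92% and 96% at 10, 15, 20 and 25 per group. Twenty is the smallest size on the grid above 80%, as the protocol states. If the effect is redrawn at each visit, 20 per group gives 76% with Sidak and 92% without. The data model is therefore a fair basis for the check.

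**Algebra under arm coding.** For arm d, visit v and covariate value x, the extended model has mean μ(d,v) + βx + g(d)x. Then

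(V1 − V0 | d, x) = μ(d,1) − μ(d,0).

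Both βx and g(d)x drop out, so no g(d) reaches the primary contrast.

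**Numerical confirmation.** In simulated complete data with a true age modifier, the primary contrast was computed without and then with the three interactions:
- three visits: 12.956 (SE 3.153) both times;
- two visits: 16.364 (SE 2.060) both times.

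**Approximate power by hand, m = 0.10, 25 per arm, three visits.**

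*Two-way term.* By the third visit both arms have had psilocybin, so the arms differ in age slope only at visit 1. Averaged over three visits the difference is 0.10 × 55 / 3 = 1.83 per SD of age.
- Psilocybin arm, mean of three visits: baseline × (1 + ⅔e), variance 13² × 1.153² + 0.153² × (55² + 13²) ≈ 300.
- Control arm: baseline × (1 + ⅓e), variance 13² × 1.077² + 0.077² × (55² + 13²) ≈ 215.
- SE of the slope difference ≈ √[(300 + 215)/25] = 4.54; ratio 1.83/4.54 = 0.40; power ≈ 7%.

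*Arm × age on V1 − V0.* The slope difference is 0.10 × 55 = 5.5.
- Psilocybin-arm variance of the change: 12.65² + 2 × (0.23 × 13)² = 177.9, plus retest noise (0.03 × 55)² = 2.7.
- Control-arm variance: 2.7.
- SE ≈ √[(177.9 + 2.7 + 2.7)/25] = 2.71; ratio 5.5/2.71 = 2.03; large-sample power ≈ 53%.

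**Simulated rejection rates, arm coding, three visits, 25 per arm.** Ranges span separate runs of 600 to 3,000 trials.

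| True modifier (points per SD of age) | Planned covariate × Drug | Covariate × arm on the change, or covariate × Drug × Visit at V1 |
|---|---|---|
| 0 | 5–7.5% | 5–7% |
| 10 | 6–8% | 42% (three-way term); 45–49% (change) |
| 15 | 8.5–10% | 75–77% (change) |
| 20 | 17% | 92% (three-way term) |

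With only V0 and V1 in the model, the 10-point row is about 11% against 55%, each with a null rate of about 7%.

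**Treatment-received coding.** With baseline as a separate undosed level and three visits, age × Drug rejects in 86–87% of trials at 10 points, and in 9–12% when there is no modification.

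**The case against.** The strongest reply is that the protocol never defines Drug. The endpoint formula attaches a drug label only at V1, and the power simulation adds the effect at psilocybin visits, which include visit 2 for controls. That is compatible with treatment received and one shared baseline. The baseline-by-psilocybin and baseline-by-placebo cells are then empty, so the Visit × Drug marginal means cannot be estimated exactly as written, but the contrasts against a shared baseline can. Under this coding the terms do not cancel. This stands: the cancellation is conditional on arm coding. That coding is still the better-supported one, because the text takes V0-to-V1 contrasts within each drug condition and calls their difference a between-group one.

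A second reply is that the extended models are given only in prose, so an interaction with drug may be shorthand for one with the Drug × Visit effect. That is possible. But the article names the terms and their purpose, and read literally they do not serve it. This is a stated choice rather than a detail left to another document.

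A reader might also infer that choosing the model by deviance test contaminates the primary result. The documents do not support this. Under arm coding with complete data the contrast and its SE do not move. Under treatment-received coding, with no mean drug effect, simulated rejection was 8.9% before and 8.7% after selection without heterogeneity of effect, and 0.9% against 1.0% with an SD of 23%. The chance of picking at least one of three null terms, 1 − 0.95³ = 14%, assumes independent tests at exactly 5%; under arm coding such a pick leaves the primary contrast unchanged. Nor does the deviance test itself leave the question unanswered: the same test applied to a three-way term would address it. The missing Visit component is the cause.

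**Conclusion.** The modifier analysis is misspecified as written under the better-supported reading, and ambiguous otherwise. With Drug as randomised arm, the planned test has about 7% power for an assumed modifier of 10 points per SD of age, little above its null rate, where a test on the change has 45–49%. With Drug as treatment received, the test does bear on modification but rejects in about 9–12% of trials when there is none.

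The cancellation is exact and needs no figures. The rejection rates rest on the protocol's simulation assumptions and on modifier sizes chosen for illustration.

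The problem is confined to a secondary question. It would be too strong to say that the stated aim cannot be met under any coding, or that the primary estimate is at risk. The sex analysis in {20b} may partly cover sex, though its form is not given. The point merits correction because age and treatment resistance have no other planned analysis and the remedy is simple.

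**What to change.** In Statistical methods {20a}:
- State how Drug is coded at each visit, baseline included.
- Name Eq. 1 as the fixed primary model, so that the deviance comparison has no bearing on which model supplies the primary contrast.
- Test each modifier separately with covariate × Drug × Visit plus all lower-order terms, reading the V1 component. Equivalently, regress the V0-to-V1 change on arm, covariate and their product. Use robust standard errors there, since the assumed variance of the change is about 181 in the psilocybin arm and 3 in the control arm.
- Report each modifier estimate with its interval, labelled exploratory, whatever the deviance result. Use the same form for the sex analysis in {20b}.

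The cost is wording only; no data collection or sample size changes. The downside is that power stays low at 25 per arm: even the assumed 10-point modifier would be missed about half the time, so a non-significant result must not be read as absence of modification.

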**Methods:**

Fifty participants diagnosed with MDD or persistent depressive disorder (PDD) will be recruited from a tertiary mood disorders clinic and undergo 1:1 randomization into either an experimental or control arm. Participants will be given either 25 mg psilocybin or 25 mg microcrystalline cellulose (MCC) placebo for the first treatment. Three weeks later, those in the control arm will transition to receiving 25 mg psilocybin. We will investigate whether treatments are associated with changes in arterial spin labelling and blood oxygenation level-dependent contrast neuroimaging assessments at acute and subacute timepoints. Primary outcomes include testing whether psilocybin demonstrates acute changes in (1) cerebral blood flow and (2) functional brain activity in networks associated with mood regulation and depression when compared to placebo, along with changes in MADRS score over time compared to placebo. Secondary outcomes include changes across complementary clinical psychiatric, cognitive, and functional scales from baseline to final follow-up. Serum peripheral neurotrophic and inflammatory biomarkers will be collected at baseline and follow-up to examine relationships with clinical response, and neuroimaging measures.

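### The exploratory biomarker regression on MADRS change names neither baseline MADRS nor arm, so a markers-only fit can show associations that do not reflect prediction of response to psilocybin

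*Protocol article*

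**What the plan says.** The exploratory hypothesis in Objectives {7} is that "our baseline blood-based biomarkers of interest will predict treatment response (i.e., changes in depression scores) measured over time by the MADRS". Outcomes {12} likewise says the markers (BDNF, CRP, S100B) "will be measured in blood at baseline and subsequently evaluated as predictors of treatment response".

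The analysis is one sentence in {20a}, under which regression is used to "assess the relationship between baseline and change in peripheral biomarker measures and post-treatment change in MADRS scores". This fixes the outcome (MADRS change) and the marker terms. It lists no covariates and excludes none.

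Objectives {7} makes two further predictions that bear on this model:
- "It is predicted that these biomarkers will be associated with MADRS scores at baseline".
- "It is expected that there will be a post-treatment increase in BDNF and a reduction in CRP and S100B plasma levels".

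Other facts that matter here:
- Allocation is 1:1 with 25 per arm, and both arms receive psilocybin at Treatment Visit 2, three weeks after the first treatment (Trial design {8}, Sample size {14}).
- Blood sampling is optional (section {26b}), so fewer than 50 may contribute.
- The abstract says that "biomarkers will be collected at baseline and follow-up to examine relationships with clinical response", whereas Outcomes {12} names baseline only. The readable text gives no date for the follow-up sample.

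**The concern.** Three separate issues arise if the model is fitted with marker terms only.

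1. **Baseline marker.** A marker that tracks baseline severity will correlate with change from baseline whenever the slope of follow-up on baseline MADRS differs from 1, even if it adds nothing to baseline MADRS as a predictor. The protocol itself predicts that marker–severity link.
2. **Marker change.** If psilocybin moves the markers and lowers MADRS, the two changes correlate across pooled arms even with no link between them within an arm. This applies only while the arms differ in treatment.
3. **Meaning.** Even a real association, adjusted for baseline MADRS and arm, is prognostic. Without a marker-by-arm term it does not separate response to psilocybin from improvement under placebo.

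The article gives early prediction of treatment response as an aim of the trial. A marker could be carried forward on an association of the first or second kind, or a prognostic marker could be described as predicting response to psilocybin.

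**Working it through.** **The plan's own figure.** No alpha, power or effect size is stated for the biomarker analysis. The only sample-size result, 20 per group for over 80% power on the CBF contrast, reproduces (simulated mixed model with Sidak for three contrasts: 81% at 20 per group), but it does not bear on this point.

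**Inputs.** From the document: N = 50, 25 per arm. N = 30 is also run because blood is optional. Assumed, because the document gives none: marker–baseline MADRS correlation r; baseline–follow-up MADRS correlation ρ; ratio k of follow-up to baseline MADRS SD; arm effects in SD units; two-sided 5% test.

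**A. Baseline marker against MADRS change, with no marker effect given baseline MADRS.** Set the baseline SD to 1. The within-arm SD of change is s = √(1 + k² − 2ρk). With an arm effect of 0.8 s on MADRS change, the pooled SD is s√(1 + 0.8²/4) = 1.077 s. The expected correlation is

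c = r(ρk − 1) / (1.077 s),

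and the rejection rate is approximately P(Z > 1.96 − z) + P(Z < −1.96 − z), with z = atanh|c| × √(N − 3).

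Example with r = 0.3, ρ = 0.5, k = 1: s = 1, c = −0.15/1.077 = −0.139, z = 0.140 × √47 = 0.96, rejection 16%.

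Simulation (2,000 datasets per row, N = 50):

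| r | ρ | k | Formula, marker only | Simulated, marker only | Simulated, baseline MADRS and arm added |
|---|---|---|---|---|---|
| 0.2 | 0.5 | 1 | 10% | 9% | 4% |
| 0.2 | 0.3 | 1 | 12% | 11% | 5% |
| 0.3 | 0.5 | 1 | 16% | 15% | 4% |
| 0.3 | 0.3 | 1 | 21% | 20% | 5% |
| 0.5 | 0.5 | 1 | 37% | 38% | 5% |
| 0.5 | 0.3 | 1 | 49% | 50% | 6% |
| 0.5 | 0.5 | 1.5 | 9% | 9% | 5% |
| 0.5 | 0.5 | 2 | 5% | 5% | 5% |

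The last row shows no inflation because the slope ρk is then 1. At N = 30 the highest marker-only rate is 33%. Adding baseline MADRS alone restores about 5%; adding arm alone does not. With r = 0, the model without arm rejects in 4–6%: a baseline marker is independent of randomised arm, so omitting arm does not inflate its test.

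**B. Marker change against MADRS change, arms pooled, no link within arm.** With arm effects d₁ and d₂ on the two changes (within-arm SD 1), the size of the pooled correlation is

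|c| = (d₁d₂/4) / √[(1 + d₁²/4)(1 + d₂²/4)].

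At N = 50:
- Both 0.5: c = 0.0625/1.0625 = 0.059, z = 0.40, rejection 7% (simulations 6–7%).
- Both 0.8: c = 0.16/1.16 = 0.138, z = 0.95, rejection 16% (simulations 15–17%).
- Both 1.0: c = 0.25/1.25 = 0.20, z = 1.39, rejection 28% (simulations 28–30%).

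With arm in the model the rate is about 5% throughout.

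**C. Prognostic or specific to psilocybin.** This needs no arithmetic. A marker main effect describes the average association over both arms. Only a baseline marker × arm term compares the association under psilocybin with that under placebo.

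**The case against.** The strongest reply is that the gap is silence. One sentence in a condensed article on an exploratory analysis does not fix the covariates, and an analysis plan, not shown here, commonly lists them. A reader might infer that baseline MADRS and arm are excluded; the text does not say so. Nor is a change-score outcome wrong in itself: once baseline MADRS is in the model, the marker coefficient is the same whether the outcome is change or the follow-up score.

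This limits the point but does not remove it. The same section lists model terms for CBF (age, sex, drug, drug by visit) and adds drug interactions for age, sex and prior failed treatments to study effect modification. For the biomarkers it names only marker terms, beside hypotheses that create both problems.

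Other parts of the reply also stand:
- The two mechanisms act on different predictors. The shared drug effect does not touch the baseline-marker hypothesis, and it weakens once both arms have had psilocybin.
- The sizes are assumed. Entry requires HAMD-17 above 17, which restricts baseline severity and may hold r down, and a larger follow-up SD reduces or removes the inflation.
- The protocol defines response as change in depression scores, so specificity to psilocybin is a further question. The marker-by-arm term is needed only for a claim about psilocybin versus placebo.

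**Conclusion.** The point holds as a weakness of the model as written. If fitted with markers only, the baseline-marker test can reject through regression to the mean (about 5% to 50% at N = 50). While the arms differ, the marker-change test can reject through the shared drug effect (about 6–7% at 0.5 SD on both variables, about 28–30% at 1.0 SD). These ranges rest on assumed correlations, SD ratios and arm effects. The directions follow from the protocol's own predictions, with the marker shift read as an effect of psilocybin relative to placebo.

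A reader might go further and infer that any significant result would be an artefact, or that the hypothesis would be declared supported regardless. The documents support neither. Confounding does not exclude a real association, nearly all the computed rates are below one half, and no decision rule is stated. The analysis is exploratory, but the remedy uses data already planned and costs little, so the change is worth making before analysis.

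**What to change.** In {20a}, replace the biomarker sentence with a specification along these lines:

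- **Baseline marker.** Regress week-3 MADRS (or MADRS change to week 3), rated before the second dose, on baseline MADRS, randomised arm and the baseline marker. Report the adjusted marker effect as prognostic.
- **Specificity to psilocybin.** Add baseline marker × arm and report it with its confidence interval as the exploratory estimate behind any claim of predicting response to psilocybin versus placebo. It should not be the sole pass/fail criterion.
- **Marker change.** Use a separate model with baseline MADRS and arm, interpreted as an association. Marker change is measured after randomisation, so neither it nor its product with arm can show prediction of response. State when the follow-up sample is drawn relative to Treatment Visit 2.

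No new data are needed, only a few lines of analysis wording. The cost is a few degrees of freedom and an interaction estimate that will be imprecise, and often inconclusive, at N of 50 or fewer.
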